#### 2. Secondary outcome (Associations between muscle characteristics and exercise response).

i) Linear regression analyses will be conducted for each characteristic, e.g., muscle morphology (marker: DSM-BIA, physiological cross-sectional area and pennation angle), mitochondrial function (marker: Basal respiration; Leak respiration; NADH-linked respiration, Succinate-linked respiration, Maximal Oxidative Capacity; Maximum uncoupled respiration), and inflammation (markers: IL-6; IFN-γ; IL-17; IL2; IL-4; IL-10 and TNF-α). The change in muscle strength (T1 – T0) will be the dependent variable, and each muscle characteristic will serve as the independent variable.ii) To explore whether associations between muscle characteristics and exercise response differ by exercise modality, models will be extended by including exercise group and interaction terms (muscle characteristic × exercise group). Given the exploratory nature of the study and the limited sample size, these analyses are intended to identify potential signals rather than provide definitive evidence of effect modification. Interaction estimates will be interpreted cautiously, with emphasis on estimated effect sizes and 95% confidence intervals rather than statistical significance testing.iii) Adjusting for covariates. All models will be adjusted for the minimization factors (gender and disease type) and prespecified covariates (age and BMI). Given the exploratory nature of the study and the available sample size, the number of covariates will be restricted to reduce the risk of model overfitting..iv) Aforementioned steps will be repeated with other clinical outcomes (isokinetic muscle endurance, 6MWT, SPPB physical function and pain) as the dependent variables to address the secondary objective of the study.

Missing data will be addressed using the Multivariate Imputation by Chained Equations (MICE) method when data were assumed to be Missing Completely at Random (MCAR) or Missing at Random (MAR). Variables with substantial missingness (>30%) or data deemed Missing Not at Random (MNAR) will be excluded. Analyses on imputed data will be compared with the original dataset to assess consistency.

Analyses will be based on the intention-to-treat principle (ITT), in which data of all participants will be analyzed according to group assignment. In addition, per-protocol analysis will be performed including only those participants that performed 80% or more sessions.

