**For all patients:**
Age 50–80 years
Willingness and motivation to exercise
Low muscle strength represented by hand grip strength (HGS) <27 kg (males) and <16 kg (females). If HGS is not possible due to pain or joint deformity, use chair stand test (>15s or inability without arms) [56]
Gait speed >0.8 m/s to exclude severely disabled patients [56]

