**Sarcopenia patients:**
Sarcopenia without arthritis or other joint diseases according to the EWGSOPII criteria [56] of low muscle strength defined as HGS < 27 kg and <16 kg for males and females respectively (dynapenia). This group will primarily involve participants with probable sarcopenia (dynapenia) but may also encompass participants with confirmed sarcopenia (appendicular muscle Lean Mass (ALM)/height2 < 7.0 kg/m^2^ for males and <5.5 kg/m^2^ for females) as this is not a selection criterion. Severe sarcopenia will be excluded (gait speed <0,8 m/s)

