### Procedures overview

Fig 2 provides an overview of the trial logistics. RA patients will be recruited from the Department of Rheumatology at both Reade and Amsterdam University Medical Center (location AMC). Newly referred OA patients to the Department of Rehabilitation at Reade will be invited to participate. Additionally, OA patients from an existing OA cohort at Reade, who have previously consented to be contacted for future research, will be informed about the study via email. These include patients who received treatment at Reade between 2020 and 2023. SARC patients will be recruited from the Department of Rehabilitation Medicine at the Amsterdam University Medical Centre. Patients with RA, OA, or SARC, who are deemed eligible for participation by their medical doctor (rehabilitation physician or rheumatologist) and meet the study criteria will be informed about the study by their specialist. Interested patients will receive an information letter and an IC form from their physician. Subsequently, the investigator will contact these patients by phone after one week to provide a verbal explanation of the study and to review and confirm the inclusion and exclusion criteria. If the patient expresses interest and appears to meet the criteria, an appointment will be scheduled for a screening visit with the investigator. After signing the IC form, the individual will be considered a study participant. During the screening visit, participants will perform a handgrip strength test or walk test, as both tests are indicative of general muscle strength. These tests will be used to exclude participants who are either too strong or too weak to participate (see Table 1 for inclusion criteria). Participants with moderate muscle weakness are included to ensure adequate training tolerance and to allow detection of exercise-induced improvements in muscle strength (primary outcome: peak torque). Final eligibility will be assessed by the primary investigator in consultation with a clinical team, including a rehabilitation physician and/or rheumatologist. Participant recruitment is expected to commence in January 2026 and is anticipated to conclude in August 2027. The total study duration, including follow-up and data analysis, is expected to extend beyond this period.

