
Other measures: To enable in-depth characterization of the study participants the following variables will be collected.

a. Patient characteristics: Sociodemographic and lifestyle characteristics will be assessed using a standardized questionnaire, including age, gender, height, weight, educational level, employment status, marital status, smoking and alcohol use (including duration), symptoms, and use of walking devices. Comorbidity will be assessed using the Cumulative Illness Rating Scale (CIRS) [40], administered through a semi-structured interview. Information on current medication use will be obtained from the participant’s medical record. Protein intake will be assessed using a 24-h dietary recall conducted by a trained researcher. Protein intake (g/day) will be calculated using the Netherlands Nutrition Centre database.b. Anthropometrics: Body composition will be assessed using direct-segmental multi-frequency bio-electrical impedance analysis (DSM-BIA) (Biospace Co, Korea). DSM-BIA has been validated for assessing segmental and whole-body composition against dual energy X-ray absorptiometry (DXA) [41]. Muscle mass is expressed as SMM (kg), SMM index (SMI, kg/m^2^) by dividing SMM (kg) by height squared (m^2^) [30], relative SMM (%) by dividing SMM (kg) by body weight (kg)*100, ALM/height^2^ (kg/m^2^) by dividing ALM (kg) by height squared (m^2^) and fat free mass (%).c. Disease characteristics: diagnosis will be obtained from the participant’s medical record; Radiologic severity of osteoarthritis will be assessed using Kellgren and Lawrence grade (K&L) [42].d. Performance: handgrip strength will be assessed with a JAMAR**®** Dynometer (Patterson Medical, UK) [43,44]. Participants will be seated with elbows flexed at 90 degrees, shoulders adducted and forearms in a neutral position without support. They will be instructed to squeeze the dynamometer maximally three times per hand, alternating between the right and left sides. The highest recorded value (kg) will be reported; Short Physical Performance Battery (SPPB test) [45]. The SPPB assesses lower extremity function through three components i) Balance Test: Participants perform progressively challenging standing positions (feet together, semi-tandem, and full tandem stance) for up to 10 seconds each. ii) Gait Speed Test: Walking speed is measured over a 4-meter course. iii) Chair Stand Test: Participants complete five timed chair rises without using their arms for support. The time to complete the five repetitions will be recorded in seconds. The total SPPB score (0–12) reflects overall lower limb function, with higher scores indicating better performance.e. Patient-Reported Outcome Measures (PROMs) will be measured with online questionnaires: Numeric Rating scale pain (0–10) [46], PROMIS® short forms regarding fatigue (8a) version 1.0, physical function (8b) version 2.0, ability to participate in social roles and activities (8a) version 2.0 [47]. FitMáx© survey [48] is a questionnaire consisting of three single answer questions, about the maximum capacity of walking (scale from 0–13), climbing stairs (scale 0–10) and cycling (scale 0–11). By adding the participant’s sex, age and BMI, the FitMáx© model estimates the maximum oxygen uptake, expressed in ml/kg/min [48,49].

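### SPPB is modelled as a response although entry selects on gait speed, one of its three components: a ceiling in the gait part is likely, and its size depends on a scoring key the protocol does not give

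*Protocol article*

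**What the plan says.** Three parts of the protocol article meet here.

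- **Entry.** Table 1 asks of all patients: "Gait speed >0.8 m/s to exclude severely disabled patients". The sarcopenia criteria repeat the limit: "Severe sarcopenia will be excluded (gait speed <0,8 m/s". No upper limit on gait speed is set.
- **Instrument.** Outcome measures, Other measures, item d: "The SPPB assesses lower extremity function through three components", namely balance, gait and chair stand. For gait, "Walking speed is measured over a 4-meter course"; the five chair rises are timed in seconds. The sum is bounded: "The total SPPB score (0–12) reflects overall lower limb function, with higher scores indicating better performance". The points per component and the cut-offs that turn times into points are not given.
- **Analysis.** Data analysis plan, part 2, regresses change in muscle strength on each muscle characteristic (step i), then adds exercise group and a characteristic × group interaction (step ii). Step iv extends this: "Aforementioned steps will be repeated with other clinical outcomes (isokinetic muscle endurance, 6MWT, SPPB physical function and pain) as the dependent variables". Read with step i, the SPPB outcome is change from baseline.

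The legend of Fig 2 says that follow-up repeats every baseline measure except the biopsy, so the SPPB component measurements exist at both time points.

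**The concern.** The plan selects patients on one component of a bounded score and then models improvement in that score. A patient already in the top gait category who walks faster after eight weeks gains no gait points. The real change is lost to the scale, and more often in faster walkers than in slower ones.

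The trial's stated product is effect-size estimates and mechanistic associations for later trials, with weight on estimates and confidence intervals and little on tests. A ceiling acts on those estimates. It pulls the gait component's slope on a marker, and the marker × group difference in slopes, towards zero. If baseline walking ability is related to the marker, the compression is also uneven along the marker's range. A flat SPPB association could then be read as absence of response when part of the explanation is the scale.

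**Working it through.** The protocol gives no ceiling figure for the SPPB, so there is none to reproduce. The check asks how many entrants could already be at the top of the gait sub-score.

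**Inputs from the document**
- Entry floor: gait speed > 0.8 m/s (Table 1).
- SPPB gait course: 4 m; total range 0–12; three components (Outcome measures).

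**Assumptions, not in the document**
- The gait sub-score is banded, with a top category starting at a speed c. Tried: c = 0.83, 0.90, 1.0 and 1.10 m/s.
- Baseline gait speed X is normal before the entry cut. Grid A: mean 0.95–1.2 m/s, SD 0.15–0.25. Grid B, slower walkers: mean 0.9–1.1 m/s, SD 0.15–0.20.
- Equal weights: each component carries 12/3 = 4 points, one third of the total.

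**Step 1. Time at the floor.** 4 m ÷ 0.8 m/s = 5.0 s. At the pace required for entry, every eligible patient covers the course in under 5.0 s. A cut-off of 0.83 m/s corresponds to 4 ÷ 0.83 = 4.82 s.

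**Step 2. Share already at the gait maximum.** Share = P(X > c) / P(X > 0.8).

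Worked example, mean 1.0 and SD 0.20: P(X > 0.8) = 0.841. For c = 0.90 the share is 0.691/0.841 = 82%; for c = 1.0 it is 0.500/0.841 = 59%.

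| Assumed top cut-off | Grid A | Grid B |
|---|---|---|
| 0.83 m/s | 94–100% | 91–99% |
| 0.90 m/s | 75–98% | 67–93% |
| 1.0 m/s | 44–91% | 34–77% |
| 1.10 m/s | 19–75% | 12–54% |

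Over cut-offs of 0.83–1.0 m/s the share runs from 34% to almost 100%. At 1.10 m/s it can fall to 12%.

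**Step 3. What this could do to a slope (rough illustration).** Suppose a share p of patients has its gait gain recorded as zero, and being capped is unrelated to the marker and to the true gain. The covariance of recorded gain with the marker is then (1 − p) times the true one, so the gait component's slope shrinks by the factor 1 − p. With p = 0.34 it keeps 66%; with p close to 1 it keeps almost nothing. For the total, if the three components also had equal weights and equal true slopes, the loss is p/3: 0.34/3 = 11% to 1/3 = 33%. These figures show the order of size only. Coarse bands, or capping that is related to the marker, would change them.

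**Step 4. The other components.** No entry rule sets a minimum on balance or chair stand. The fallback rule points the other way: "If HGS is not possible due to pain or joint deformity, use chair stand test (>15s or inability without arms". It admits slow chair-stand performers, who have room to improve.

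**The case against.** The strongest reply is that the document itself shows only a floor. The bands, the top cut-off, the weights and the baseline distribution all come from outside it. That stands, and it is why the size is given as a conditional range.

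A reader might infer that the gait component is at its maximum for everyone, so that a third of the score cannot register improvement. The document does not support this. Entrants between 0.8 m/s and the top cut-off can still gain; at an assumed cut-off of 1.0 m/s they could be up to 66% of the sample (100 − 34). The one-third weight is also an assumption. Nor does it follow that a flat SPPB association would be purely a scale artefact, since two of the three components have no entry floor.

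Other points on that side:
- **Measurement of the floor is not fully clear.** Table 1 gives no course length for the entry test, and Procedures overview says "participants will perform a handgrip strength test or walk test, as both tests are indicative of general muscle strength". Table 1 nevertheless binds all patients, so the truncation holds as written. The 5.0 s figure assumes that the entry pace carries over to the 4-m course.
- **The wording of step iv is loose.** A comma may be missing after SPPB, and components could be meant. The only SPPB score that the article defines is the 0–12 total, and SPPB is a dependent variable on either reading.
- **The stakes are small.** SPPB stands under Other measures, the 6MWT gives a continuous walking outcome in the same step, and the article calls the interaction analyses hypothesis-generating. This stands and sets the severity.
- **Replacing the total would drop balance.** This also stands, so the total should stay.

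**Conclusion.** The point holds in a limited form. Step iv models improvement in a bounded score after entry has truncated one of its components from below, and the article does not mention a ceiling. A ceiling in the gait component is likely. Under assumed cut-offs of 0.83–1.0 m/s and the assumed baseline distributions, about one third to nearly all entrants would start at the gait maximum. Marker-response and marker × group estimates for that component would be weakened accordingly. The effect on the total is smaller, because balance and chair stand are free of the entry floor.

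The size rests on a scoring key and a gait distribution that the document does not give. Neither the primary outcome nor the sample size is affected. Severity is low, and the point is worth acting on mainly because the uncapped measurements are already being collected.

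**What to change.** In Data analysis plan, part 2, step iv:

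1. Keep the SPPB total as a dependent variable, and say explicitly that the total is meant.
2. Add 4-m walking speed (m/s) and five-repetition chair-stand time (s) as dependent variables, using the same models.
3. Report the share of participants at maximum, for the SPPB total and for the gait component, at baseline and follow-up, by exercise group. State that a flat SPPB association will be read against these shares and the two continuous measures.
4. State how patients unable to complete the chair rises are handled in the analysis of chair-stand time.

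Cost: analysis wording only, with no added visit, test or patient. Two more dependent variables over the 16 listed markers (3 morphology, 6 mitochondrial, 7 cytokine), each with a main and an interaction model, come to 2 × 16 × 2 = 64 further fits at most in about 60 analysed patients. That is tolerable where estimates and intervals are reported as exploratory, but the number of models should be stated. The rule for patients unable to rise is the one new decision needed.

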### Trial sample size

This study was designed as an exploratory mechanistic trial because no previous studies have compared strength and endurance exercise in patients with RA, OA or SARC. Consequently, no reliable disease-specific between-group effect size was available to perform a formal a priori sample size calculation for the primary comparison. The target sample size was therefore determined pragmatically, balancing the feasibility of the extensive mechanistic assessments (including muscle biopsies, mitochondrial respirometry and inflammatory biomarker analyses) with the aim of including as many participants as possible within the available resources and study period. A total of 69 patients will be included, taking into account a 15% dropout rate, 60 patients will be analysed of which 30 will be randomized to the strength group and 30 to the endurance group, stratified by diagnosis (OA, SARC and RA) and gender. This resulted in a target sample size of 69 participants (23 per disease group). The study is intended to estimate intervention effects, variability and mechanistic associations to inform the design of future adequately powered confirmatory studies. The study is not powered for separate confirmatory analyses within each disease group.

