#### 1. Primary outcome (isokinetic muscle strength).

The effect of exercise type (strength vs. muscle endurance exercise) on isokinetic muscle strength (pre- vs. post-intervention) will be assessed using linear mixed models. Models will include fixed effects for exercise group, time (pre/post), exercise group, disease type, and gender. The time × exercise group interaction will be included to estimate differential changes in muscle strength between intervention groups. Random effects will account for individual variability.

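### The rule excluding data deemed MNAR and variables over 30% missing neither exempts outcomes nor says what exclusion means, and for outcome data it conflicts with the ITT statement

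*Protocol article*

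**What the plan says.** All places are in the protocol article.

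- **Data analysis plan, section 2 (secondary outcome), missing-data paragraph.** Multiple imputation by chained equations is used when data are assumed MCAR or MAR. Then: "Variables with substantial missingness (>30%) or data deemed Missing Not at Random (MNAR) will be excluded". The one check is: "Analyses on imputed data will be compared with the original dataset to assess consistency".
- **Same section, next paragraph.** "Analyses will be based on the intention-to-treat principle (ITT), in which data of all participants will be analyzed according to group assignment". A separate per-protocol set is defined by attendance at 80% or more of sessions.
- **Same section, item i.** The dependent variable is change in strength from baseline to follow-up, and each muscle characteristic is a predictor. Item iv repeats this for other clinical outcomes.
- **Section 1 (primary outcome).** The effect of exercise type "on isokinetic muscle strength (pre- vs. post-intervention) will be assessed using linear mixed models", with a time by group interaction.
- **Outcome measures.** The biopsy is taken before the intervention only.
- **Other process measures.** Adverse events and loss of motivation are given as examples of reasons for drop-out.
- **Trial sample size.** "A total of 69 patients will be included, taking into account a 15% dropout rate, 60 patients will be analysed".

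**The concern.** The rule has two limbs, and neither distinguishes outcomes from predictors.

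The MNAR limb depends on a judgement that the observed data cannot settle, and no criterion is given for making it. It can be invoked at any missing fraction, after the data have been seen. A missing value has nothing to remove, so exclusion must mean one of three things: not imputing, dropping the patient from that analysis, or dropping the variable. The text does not say which. For an outcome, the first two leave the change-score regressions on patients who completed follow-up, in the situation where completers are most open to question. The third removes the analysis. Each sits badly with analysing the data of all participants as assigned.

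The stated check does not fill the gap. It compares an analysis that assumes MAR with one on available cases. Agreement between the two says nothing about loss that depends on the unseen value.

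The 30% limb can remove a whole variable although most of its values exist. The mechanistic markers are the reason for the trial, and the six respirometry read-outs come from one biopsy, so they could be lost together.

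**Working it through.** **1. The plan's own drop-out figure.** Inputs: 69 enrolled, 60 analysed, 15% drop-out (Trial sample size). 60 × 1.15 = 69 gives the stated number; 60 / 0.85 = 70.6, or 71, is the usual inflation. The two-patient difference is immaterial here. The figure used below is 15%, the only rate of loss the document gives.

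**2. When the 30% limb applies.** 0.30 × 69 = 20.7, so 21 missing (21/69 = 30.4%) triggers it while 69 − 21 = 48 values exist. With X ~ Binomial(69, p), the chance that X ≥ 21 is:

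| True missing rate p | P(X ≥ 21) |
|---|---|
| 15% (planned drop-out) | 0.1% |
| 20% (assumed) | 2.6% |
| 25% (assumed) | 18% |
| 30% (assumed) | 51% |

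For a variable that needs follow-up, an assumed further technical loss f gives a total of 1 − 0.85(1 − f):

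- f = 10%: 23.5% missing, 11% chance of exclusion
- f = 15%: 27.8% missing, 35% chance
- f = 20%: 32.0% missing, 65% chance

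The biopsy is baseline only, so follow-up drop-out does not add to its missingness.

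**3. What completers can misstate for an outcome.** Let ρ be the correlation between the tendency to drop out and the change in the outcome. With a fraction d lost, the completers' mean shifts by ρ·φ(z_d)/(1 − d) SD of change. If loss is informative in one arm only (assumed):

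- d = 15%: 0.233/0.85 = 0.274, giving 0.08 SD (ρ = 0.3), 0.14 SD (ρ = 0.5) and 0.27 SD (ρ = 1)
- d = 20% in the informative arm: 0.280/0.80 = 0.350, giving 0.105, 0.175 and 0.35 SD

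If loss is equally informative in both arms at 15%, the shifts cancel and the between-arm bias is about zero. A simpler version assumes drop-out of 20% versus 10%, with drop-outs 0.5 to 1.0 SD worse in both arms: (0.20 − 0.10) × 0.5 = 0.05 SD, up to 0.10 × 1.0 = 0.10 SD.

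For scale, the standard error of the difference at 30 per arm is √(1/30 + 1/30) = 0.26 SD. The 15% one-arm case is thus about 0.3 to 1.1 standard errors, and the simpler case 0.2 to 0.4.

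**4. Predictors behave differently.** Take a true slope of 0.50 with the lowest 35% of predictor values missing (simulated, normal data). Complete-case regression returns 0.50; imputing the predictor under MAR returns about 0.56. When a predictor is missing because of its own value, leaving it unimputed does not bias the slope.

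**5. The passages side by side.** One paragraph excludes data on a judgement of MNAR with no outcome exempted; the next says all participants' data are analysed. For an outcome judged MNAR, both can hold only if exclusion means from imputation and the analysis still admits patients with a baseline value alone. The mixed model can do that. The change-score regressions cannot.

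**The case against.** The sentence stands between one on when imputation is used and one comparing imputed with original data, so it can naturally be read as excluding from imputation only. On that reading, the 48 observed biopsies stay in an available-case analysis. The mixed model can already use baseline values from patients without follow-up. A fixed threshold limits discretion. The trial is openly exploratory, and an SAP may hold the criteria and sensitivity analyses.

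Much of this stands. The milder reading is possible, though the text does not establish it. The mixed model does protect the primary comparison under MAR, unless the rule is applied to it. Missing sensitivity analyses alone would not be a finding. But this is a stated rule, and an SAP would have to reinterpret or reverse it for outcomes.

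A reader might infer more: that the rule deletes the mechanistic variables, biases their associations, and breaches ITT throughout. The document does not support that:

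- It gives no missingness rate for biopsy, respirometry, ultrasound or cytokine data, and planned drop-out is half the threshold.
- ITT concerns randomised patients and their outcomes. Dropping a baseline predictor from an exploratory model loses a planned analysis but does not breach ITT.
- For a predictor missing because of its own value, declining to impute is defensible, and MAR imputation is the worse choice.

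Nor do the bias figures isolate harm caused by the rule. A mixed model valid under MAR would also be biased under MNAR, which is why a sensitivity analysis is needed.

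**Conclusion.** The point holds for outcome data. The rule is stated, exempts no outcome, gives no criterion for deeming data MNAR and leaves the meaning of exclusion open. Applied to outcomes, it rests the change-score analyses on completers and conflicts with the ITT statement, and the planned comparison of imputed with original data would not show the effect.

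The possible size is 0.08 to 0.27 SD in the arm difference, up to about one standard error at 30 per arm. This assumes 15% drop-out that is informative in one arm only; with equally informative loss it is about zero.

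For the mechanistic markers the risk is conditional. Exclusion becomes likely only if missingness nears 30%, a rate the document neither states nor implies; at 15% the chance is about 0.1%. The concern there is losing a planned analysis, not an ITT breach. This is an inexpensive improvement to the wording and does not invalidate the design.

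**What to change.** Replace the exclusion sentence in section 2 of the data analysis plan with wording to this effect:

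- No outcome data are excluded because they are suspected to be MNAR.
- Every randomised patient with any measurement stays in the section 1 mixed model, which is valid under MAR.
- For outcomes, a prespecified delta-adjusted imputation is run as a sensitivity analysis, lowering imputed changes over a stated range (for example 0 to 1 SD) separately by arm.
- Markers more than 30% missing, or suspected MNAR, are not imputed under MAR. Their available-case association is reported with the missing fraction.
- Any cytokine value below the assay limit is treated as left-censored, not as missing.

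Deleting the sentence without the fourth item would bring MAR imputation back for markers where it may bias the slope.

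The cost is analysis wording, one extra sensitivity analysis and wide intervals for sparse markers. Recruitment, visits and sample size do not change.
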